#### Phase I Dose Escalation

The phase I study is designed to end if the rate of DLTs within 90 days from the start of treatment is 33% or higher. For each dose level cohorts, a total of seven to fifteen patients will be enrolled. If zero out of the first seven with 90 day follow-up, two or fewer out of the first nine with 90 day follow-up, three or fewer out of the first twelve with 90 day follow-up, or four or fewer out of the first fifteen of patients with 90 day follow-up experience a DLT as defined above, then the dose will escalate to the next dose level. If three or more of the first nine patients, four or more of the first twelve, or five or more of the first fifteen patients experience a DLT, then the MTD will be considered to have been exceeded. The MTD will be defined as the immediately previous lower dose level tolerated.

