#### Phase I Waiting Periods

Dose escalation on the phase I portion of this study should not occur until a sufficient waiting period has occurred after patients have been treated. A period of 90 days must pass in order to assess toxicity. If 90 days have transpired without DLT in each of the first seven (7) patients enrolled to a specific dose level, then dose escalation to the next level may proceed. Patients will continue to be enrolled to each dose level (up to a maximum of 15 patients) with ongoing assessment of those reaching 90 day follow-up so long as either criteria for defining the MTD or criteria for further dose escalation is not reached. If fifteen patients are enrolled to a given dose level yet criteria for adequate follow-up are not reached in a representative sample of patients, further enrollment to the protocol will be suspended until adequate follow-up is reached.

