### **10.2 Sample Size and Accrual**

While accrual realities may limit total enrollment to only 7 patients per dose level, the investigators will attempt to enroll up to 15 patients per dose level in an effort to both improve the toxicity determination as well as afford some evaluation of efficacy. The sample size of the phase I component of this study will not exceed 60 patients.

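### Section 10.1 settles every dose level at nine evaluable patients at the latest, yet keeps limits at 12 and 15; if more than nine are treated, escalate and MTD exceeded can both be met with no precedence stated

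*Protocol*

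**What the plan says.** Protocol section 10.1, Phase I Dose Escalation, states the aim first: the study "is designed to end if the rate of DLTs within 90 days from the start of treatment is 33% or higher". It then gives the cohort size per level as 7 to 15.

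The dose goes up on any of four results, joined by *or*:
- at seven patients followed for 90 days, no DLT at all;
- at nine and at twelve patients, "two or fewer out of the first nine with 90 day follow-up, three or fewer out of the first twelve with 90 day follow-up";
- at fifteen patients, no more than four DLTs.

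The MTD counts as exceeded on any of three: "If three or more of the first nine patients, four or more of the first twelve, or five or more of the first fifteen patients" have a DLT.

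The next subsection, Phase I Waiting Periods, governs accrual within a level: "Patients will continue to be enrolled to each dose level (up to a maximum of 15 patients". It makes this conditional on neither the MTD criterion nor the escalation criterion having been met. Section 4.1.1, Dose Escalation, says the same. Both also foresee 15 patients being enrolled at a level before follow-up is adequate. Section 10.2 says the investigators will try to reach 15 per level, to sharpen the toxicity estimate and learn something about efficacy. Section 7.4 gives no stopping rule of its own and refers back to 10.1.

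**The concern.** Seven limits are stated: four for escalation and three for exceeding the MTD. They read like a staged design in which unclear results at one look pass to the next. No such middle zone exists at nine, so it is unclear what the looks at 12 and 15 are for.

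The protocol also expects accrual to run past nine while earlier patients complete their 90 days. The later looks may then be applied to a level that the nine-patient look has already settled, and they may disagree with it.

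This is the only decision rule for the primary endpoint, and through section 7.4 it is also the stopping rule. Two teams following the same text on the same data could reach opposite conclusions about whether a level was tolerated.

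**Working it through.** **Inputs (section 10.1).** Escalate on 0/7, ≤2/9, ≤3/12 or ≤4/15. Exceeded on ≥3/9, ≥4/12 or ≥5/15. The protocol gives no true DLT rate, so p is an assumption, varied from 10% to 50%.

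**The plan's own figure.** 3/9 = 4/12 = 5/15 = 33.3%. Each exceeded limit, taken alone, matches the stated 33%.

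**Step 1: undecided counts at each look.**

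| Patients | Escalate | Exceeded | Undecided |
|---|---|---|---|
| 7 | 0 | none stated | 1 to 7 |
| 9 | 0 to 2 | 3 to 9 | none |
| 12 | 0 to 3 | 4 to 12 | none |
| 15 | 0 to 4 | 5 to 15 | none |

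With no undecided count at nine, and enrolment continuing only while neither criterion is met, the level is settled at nine evaluable patients at the latest (at seven if 0/7). The four limits at 12 and 15 have no role when the looks are taken in sequence. This holds at any DLT rate.

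**Step 2: both criteria met when more than nine are treated.**
- 2/9 (escalate), then 5/15 (exceeded).
- 0/7 (escalate), then 4/12 (exceeded).
- 3/9 (exceeded), then 4/15 (escalate).

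**Step 3: how often, if all 15 are treated.** Let k be the DLTs in the first nine, c those in patients 10–12 and d those in patients 13–15, all independent binomial with rate p.

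- A (escalate at nine, exceeded later) = Σ over k = 0..2 of P(k) × P(k+c ≥ 4 or k+c+d ≥ 5).
- B (exceeded at nine, escalate later) = Σ over k = 3..4 of P(k) × P(k+c ≤ 3 or k+c+d ≤ 4).

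Worked at p = 0.20:
- A = 0.1342×0.0016 + 0.3020×0.0211 + 0.3020×0.1480 = 0.051.
- B = 0.1762×0.7086 + 0.0661×0.2621 = 0.142.
- For k = 3 the second factor is P(c=0) + P(c=1)P(d=0) = 0.512 + 0.384×0.512 = 0.7086. For k = 4 it is 0.8⁶ = 0.2621.

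| Assumed true rate | A | B | Conflict, A + B |
|---|---|---|---|
| 10% | 0.7% | 4.4% | 5.1% |
| 20% | 5.1% | 14.2% | 19.3% |
| 33% | 10.4% | 13.7% | 24.0% |
| 50% | 5.6% | 3.2% | 8.8% |

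(Rows are rounded separately.) The nine-patient look always gives a verdict, so A + B is also the probability that both criteria are met somewhere among the 15.

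**The case against.** The fairest defence is that the limits were never meant as a strict sequence. They are joined by *or*, and assessment is described as ongoing, so the tier might simply be the one that matches the number evaluable at the review. On that reading the 12- and 15-patient limits can be used. This stands as a possible intention, but the text does not say it, and it does not settle what happens when a verdict at nine and a verdict at 15 differ. Confirmation of DLTs by the study chair and the DSMC does not help either: it decides whether an event is a DLT, not which look governs.

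Several stronger readings are tempting, and the document does not support them:

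- *Every level is decided at exactly nine.* No: 0/7 decides at seven.
- *DLTs in patients 10–15 are ignored.* Section 10.1 counts them expressly in the limits at 12 and 15. What is missing is precedence.
- *No more than nine per level, or 27 over three levels, can be treated.* Nine is the last sequential decision point. Sections 4.1.1 and 10.1 allow more patients to accrue during the 90-day wait.
- *The overall maximum is wrong.* "The sample size of the phase I component of this study will not exceed 60 patients" is an upper bound. It may be loose, but it is not false.
- *The rule fails its 33% aim because it escalates too often at that rate.* At a true rate of 1/3, P(escalate) is 0.38, 0.39 and 0.40 at 9, 12 and 15 patients, each look taken alone. That is how a 33% observed-rate limit behaves in small samples, whichever look governs.

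**Conclusion.** The point holds. The individual limits agree with the 33% target; the fault is in how they are combined. The outcomes at nine are exhaustive, the limits at 12 and 15 have no sequential function, and the accrual text permits, and section 10.2 seeks, the cohort sizes at which the criteria can contradict each other.

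The logical part needs no assumed rate. It assumes that the same nine patients are counted on both sides. Escalation refers to patients with 90-day follow-up and the MTD criterion to the first nine patients, so a loss before day 90 could make the two sets differ. That is a further ambiguity, not a designed route to the later looks.

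The conflict probabilities of about 5% to 24% depend on the assumed DLT rate, on independence between patients and on all 15 being treated. They show that the conflict would not be rare at rates near the target, but they do not forecast this trial. Because the protocol itself fixes this rule, for the primary endpoint and for stopping, it should be corrected in the protocol.

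**What to change.** Reconcile the Dose Escalation text in 4.1.1, both Phase I subsections of 10.1, and 10.2.

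1. Replace the two rule sentences in 10.1 with one table giving mutually exclusive outcomes at 7, 9, 12 and 15 patients.
2. State which look is binding.
3. State which patients count at the decision date, including any treated beyond nine and any without 90 days of follow-up.
4. State which criterion prevails when both are met at the same level.
5. Either give the looks at 12 and 15 a working role or remove them, and make the cohort size in 10.2 agree.

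The choice of rule is the sponsor's. The cost is protocol wording and one table.

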#### Phase I Waiting Periods

Dose escalation on the phase I portion of this study should not occur until a sufficient waiting period has occurred after patients have been treated. A period of 90 days must pass in order to assess toxicity. If 90 days have transpired without DLT in each of the first seven (7) patients enrolled to a specific dose level, then dose escalation to the next level may proceed. Patients will continue to be enrolled to each dose level (up to a maximum of 15 patients) with ongoing assessment of those reaching 90 day follow-up so long as either criteria for defining the MTD or criteria for further dose escalation is not reached. If fifteen patients are enrolled to a given dose level yet criteria for adequate follow-up are not reached in a representative sample of patients, further enrollment to the protocol will be suspended until adequate follow-up is reached.

### **10.2 Sample Size and Accrual**

While accrual realities may limit total enrollment to only 7 patients per dose level, the investigators will attempt to enroll up to 15 patients per dose level in an effort to both improve the toxicity determination as well as afford some evaluation of efficacy. The sample size of the phase I component of this study will not exceed 60 patients.

### **10.3 Data Analyses**

#### Data Analysis Plans

Interim Reports: Interim reports will be prepared every twelve months from time of enrollment of first patient until enrollment is complete. In general, the interim reports will contain information about patient accrual rate with projected completion dates of the trial, status of QA review and compliance rate of treatment per protocol, and the frequencies and severity of toxicity.

The dose-limiting toxicity (DLT) and the maximum tolerable dosage (MTD) will be determined based on this Phase I design. The assessment of safety will be mainly based on the frequency of adverse events. The incidence of AEs together with the 95% confidence interval will be reported. The overall complete response rate and corresponding 95% confidence interval will be presented. Various survival rates such as local control, recurrence free survival, and distant disease-free interval will be computed using Kaplan-Meier curves along with the 95% confidence interval. Exact binomial method will be used to calculate the response rate, toxicity and the corresponding 95% confidence interval.

- Kaplan-Meier method will used to estimate the distant disease-free interval.

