### 1.3 Study Rationale

Given interest in preoperative S-PBI, there have been several recently initiated preoperative S-PBI trials that have opened and are ongoing (see Table 1). However, these ongoing preoperative trials are predominantly using doses seen in the adjuvant setting as established with IORT, primarily 21Gy/1Fx, although a 3-fraction and 5-fraction regimen are also currently being investigated at Moffit (NCT03137693) and the Juravinski Cancer Center (NCT02065960), respectively. Pathologic complete response rates with three-fraction preoperative S-PBI have been reported to be 36%, with the highest pCR rate of 67% in the 25.5Gy/3Fx cohort, though this cohort was small with only 6 patients (Bondiau IJROBP 2013), suggesting room for improvement. At ESTRO in 4-2019, the results from the Netherlands (clinical trials.gov: NCT0231661) ABLATIVE trial treating patients with Estrogen positive her2- tumors and 20 Gy preoperative radiation yielded a path CR of 33% at 6 months and 41% at 8 months with mild treatment toxicity (ESTRO abstract OC-0591 Vasmel et al.)

As predicted by the universal survival curve, 38Gy/1Fx would be equivalent to 70Gy/35Fx, a dose that is typically used for gross disease (Park IJROBP 2008). Given that these early studies have reported minimal toxicity with the addition of preoperative S-PBI, this offers promise that further dose escalation to achieve a radioablative dose adequate for gross disease may be feasible.

Therefore, the purpose of this phase I trial is to evaluate dose-limiting toxicity while dose escalating single-fraction preoperative S-PBI to a presumed radioablative dose over 3 cohorts, starting with 30Gy in 1 fraction and advancing to 34Gy and 38Gy in 1 fraction. This would be accomplished on the MR Linac, CyberKnife, or GammaPod. The GammaPod is a novel device dedicated to S-PBI utilizing a Cobalt-60 source (Yu Med Phys 2013), which offers a highly reproducible prone setup with a mean of 1.8mm of mismatch reported in 15 patients at the University of Maryland on consecutive scans (Yu JCO 2011). Implications of this research are far reaching, including determination of the maximally tolerated dose for preoperative S-PBI, pathologic complete response rates of early stage breast cancer to a predicted radioablative dose, radiographic markers of treatment response (radiomics), and translational research assessing mechanisms of immune and radiation response.

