## 4.3 Concomitant Medications/Treatments

### 4.3.1 Systemic and Adjuvant Surgery

#### Systemic Therapy

Use of endocrine therapy after pre-operative radiation should be started within 21 days after pre-operative radiation, but it is encouraged to start the day after the post-radiation biopsy. Typically, for estrogen/progesterone positive patients, many will start endocrine therapy as they are waiting for surgery. Oncotype or Mammprint studies should be done on the biopsy specimen, if possible, prior to delivery of radiation if there is adequate tissue. If not, patient may require another biopsy to obtain this tissue and this will be at the discretion of the medical oncologist.

Surgery: Surgery can be done anytime from 8 to 52 weeks at the discretion of the surgeon. Sentinel lymph node biopsy can be done at time of lumpectomy or if patient prefers mastectomy.

Sentinel lymph node mapping: in the previous University of Maryland pre-operative study there were no instances of failed sentinel lymph node mapping on the 25 patients treated on the trial. Based on this experience, we have no reason to think that there should be an increase in failed mappings with the pre-operative radiation treatment. A peri-tumoral, intra-dermal or peri-areolar injection are allowed based on the discretion of the breast surgeon.

Sentinel lymph node mapping exclusions: In the elderly population (defined differently in by different trials and also based on medical comorbidities), a sentinel lymph node procedure is often not performed on low-risk patients. In this trial, we will not require women 70+ to have a sentinel lymph node mapping if it is deemed unnecessary by their treatment team. This must be documented in the patient's medical record.

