## 6.0 MEASUREMENT OF EFFECT

### 6.1 Antitumor Effect - Solid Tumors

#### 6.1.1 Definitions

Evaluable for toxicity. All subjects will be evaluable for toxicity from the time of their first treatment with study therapy.

Evaluable for objective response. Only those subjects who have measurable disease present at baseline, have received radiation, and have had their disease re-evaluated will be considered evaluable for response. These subjects will have their response classified according to the definitions stated below. (Note: Subjects who exhibit objective disease progression prior to the end of cycle 1 will also be considered evaluable.)

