#### Secondary Endpoints

Secondary endpoints for the phase I portion of this study include cosmetic outcome as evaluated by patient and physician. In addition, the following endpoints will be evaluated as secondary endpoints:

- Local Control
- Acute Toxicity (90 Days)
- Late Toxicity (24 months)
- Rates of Surgical Morbidity
- Pathologic Complete Response Rates
- Patient and Physician Cosmesis Outcomes
- Distant Disease-Free Survival

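### Section 10.3 names only an overall complete response rate, although the protocol's interest is pCR at the predicted radioablative dose; report pCR by dose level as well

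*Protocol*

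**What the plan says.** Protocol 10.1 lists "Pathologic Complete Response Rates" among the secondary endpoints; it is the only complete-response measure there. Section 10.3 fixes the summary: "The overall complete response rate and corresponding 95% confidence interval will be presented". It adds the method: "Exact binomial method will be used to calculate the response rate, toxicity and the corresponding 95% confidence interval". No section states a response rate by dose level or by time from radiation to surgery.

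Other sections show why dose matters for this endpoint. Section 1.3 counts among the implications of the research "pathologic complete response rates of early stage breast cancer to a predicted radioablative dose", and identifies that dose: "As predicted by the universal survival curve, 38Gy/1Fx would be equivalent to 70Gy/35Fx". Section 10.1, on the therapeutic nature of the trial, says that the MTD may not be the best dose and that response information will be collected. Section 10.2 aims for up to 15 patients per level, partly to allow some look at efficacy.

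On timing, section 4.3.1 states: "Surgery can be done anytime from 8 to 52 weeks at the discretion of the surgeon". Endocrine therapy is to start within 21 days of radiation. Section 1.3 reports that another single-dose trial, at 20 Gy, "yielded a path CR of 33% at 6 months and 41% at 8 months".

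**The concern.** A single rate over all treated patients is an average of the dose-level rates, weighted by how many patients each level happens to enrol. Those numbers (7 to 15 per level) follow from DLT counts, 90-day follow-up and accrual. They were not chosen to make the average meaningful. The set of doses is not fixed either, since 30 Gy may be skipped and 26.5 Gy is used only on de-escalation.

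The pooled rate therefore equals the 38 Gy rate only if response does not depend on dose, whereas the trial escalates because a higher dose is expected to control gross disease better. A reader who takes the overall figure as the response to the ablative dose would probably read it too low, with an interval that is too narrow for that purpose. Surgery at anywhere from 8 to 52 weeks is a second mixture within the same figure, and the protocol's own citation suggests that timing may matter.

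**Working it through.** **Inputs from the protocol.** Levels of 26.5 (level -1), 30, 34 and 38 Gy, with 30 Gy skipped if the adjuvant trial shows it safe (4.1.1); 7 to 15 patients per level (10.1); at most 60 patients (10.2); exact binomial 95% intervals (10.3).

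**Assumption.** The protocol gives no expected pCR rate by dose. Three rising gradients and one flat pattern are used as a range.

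**The plan's own figure.** 4 levels x 15 = 60, which matches 10.2. No power, alpha or expected pCR is stated, so there is nothing else to reproduce.

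**Step 1: what the pooled rate estimates.** Pooled rate = sum(n x p) / sum(n) over the levels. Shortfall = 38 Gy rate minus pooled rate. Coverage is the probability that the pooled exact 95% interval contains the true 38 Gy rate, from the exact distribution of the sum of the binomials.

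| Assumed pCR at 30/34/38 Gy | Pooled, 15 per level | Shortfall | Coverage | Pooled, 30 Gy skipped (15 + 15) | Shortfall | Coverage |
|---|---|---|---|---|---|---|
| 30/40/50% | 40% | 10 points | 78% | 45% | 5 points | 93% |
| 20/35/50% | 35% | 15 points | 53% | 42.5% | 7.5 points | 89% |
| 33/50/67% | 50% | 17 points | 38% | 58.5% | 8.5 points | 87% |
| 40/40/40% | 40% | 0 | 97% | 40% | 0 | 96% |

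Example, first row: (15 x 0.30 + 15 x 0.40 + 15 x 0.50) / 45 = 18/45 = 40%; 50 - 40 = 10 points.

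**Step 2: effect of cohort sizes alone.** Under 20/35/50%:
- 15/15/15: 15.75/45 = 35.0%
- 15/7/7: (3.00 + 2.45 + 3.50)/29 = 8.95/29 = 30.9%
- 7/7/15: (1.40 + 2.45 + 7.50)/29 = 11.35/29 = 39.1%

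The pooled rate moves by about 8 points although the response at each dose is the same.

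**Step 3: how a result could look.** Suppose 3/15, 5/15 and 8/15 respond at 30, 34 and 38 Gy. Pooled: 16/45 = 35.6% (21.9-51.2%). At 38 Gy: 8/15 = 53.3% (26.6-78.7%). The 38 Gy estimate lies outside the pooled interval.

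**Step 4: timing.** The window is 52 - 8 = 44 weeks wide, and 6 and 8 months both fall inside it. Taking the cited 33% and 41% at face value, with a share w operated on at 6 months and the rest at 8 months, the rate is 33w + 41(1 - w) percent: 33% at w = 1, 37% at w = 0.5, 41% at w = 0. This is an illustration only, because the protocol gives no denominators for those figures.

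**Step 5: precision by level.** Exact 95% intervals: 5/15 gives 11.8-61.6%; 3/7 gives 9.9-81.6%; pooled 15/45 gives 20.0-49.0%.

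**The case against.** The strongest reply is that 10.3 does not say pooled, pathologic or only. Presenting an overall rate does not bar rates by level, the endpoint is worded in the plural, section 2.3.1 plans an exploratory model of pathologic response that takes treatment parameters as input, and an SAP could add a table by dose. This limits the point. Dose will be known for every patient, so nothing is lost from the data, and the defect is in the summary as written. It still stands, because the protocol does more than leave detail open: it names one summary, and that summary does not match the interest stated in 1.3 and 10.2. The exploratory model gives no rate by level.

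It is also fair that the size rests on assumed rates, is much milder if 30 Gy is skipped, and disappears if response is flat in dose.

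Some stronger readings are tempting, but the document does not support them:

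- That the trial's main efficacy result is compromised. pCR is one of seven secondary objectives, and the primary endpoint is toxicity. Section 1.3 lists pCR at the ablative dose as an implication of the research, and no objective commits to estimating it at 38 Gy.
- That cohort sizes are set by DLTs alone. Section 10.2 also names accrual and efficacy.
- That patients who decline surgery are dropped. Section 6.1.1 restricts evaluability to "Only those subjects who have measurable disease present at baseline, have received radiation, and have had their disease re-evaluated", but it defines objective response and does not mention pCR. The pCR denominator is unstated, which is a different matter from being wrongly restricted.
- That drift in surgery dates would be taken for a dose effect. A single pooled rate makes no dose comparison. That risk comes with a by-dose table, which is why the interval should be shown beside it.
- That the cited trial proves pCR rises with time. The two percentages come from another trial at 20 Gy and, as cited, carry no measure of uncertainty.

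**Conclusion.** The point holds in a limited form. As written, 10.3 produces a mixture over whichever doses are treated, with weights that have no clinical meaning, while the protocol's stated interest is response at the ablative dose. Over the assumed gradients 30/40/50% to 33/50/67% with 15 per level, the pooled rate is 10 to 17 points below the 38 Gy rate, and its 95% interval contains that rate 38% to 78% of the time. If 30 Gy is skipped, the shortfall is 5 to 8.5 points and coverage 87% to 93%. If response is flat in dose, there is no bias. The rates by dose are assumptions, and the calculation presumes that 38 Gy is reached.

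The consequence is confined to a secondary, descriptive endpoint. Dose escalation and the MTD do not depend on it, and nothing here bears on the permitted timing of surgery.

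**What to change.** In Protocol 10.3:

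- Report the pCR rate for each dose level treated, with its exact 95% interval, and keep the overall rate as a supplement labelled as pooled over dose levels.
- List the radiation-to-surgery interval descriptively alongside pCR, by dose level.
- State the pCR denominator, for example all irradiated patients with those not operated on counted as having no pCR, and an operated-only analysis as sensitivity.
- If a model with dose and interval is wanted, label it exploratory. With at most 60 patients in sequential cohorts it cannot carry more than that.

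The cost is wording only: dose is assigned, and surgery is a scheduled point in the section 5.4 table. The drawback is imprecision. With 15 patients an interval is about 50 points wide (61.6 - 11.8 = 49.8), and with 7 about 72 (81.6 - 9.9 = 71.7), against 29 for 45 pooled patients (49.0 - 20.0). The narrower pooled interval describes a different quantity, so the width is an honest account of what each level can show.
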